**Demographic and baseline clinical characteristics (once at registration/ArthritisPower)**			
	Age	Date of birth	
	Gender	Male or female	
	Race	American Indian or Alaskan Native, Asian, Black or African American, Native Hawaiian or other Pacific Islander, Caucasian, multiple race, RTA^a^	
	Hispanic ethnicity	No, unknown, yes	
	Zip code	5-digit US postal code	
	Condition(s)	Rheumatoid arthritis	
	Years since RA^b^ diagnosis	—^c^	
	Rheumatologist name	National Provider Identifier lookup by city, state	
	Height	—	
	Weight	—	
	Current medications, supplements, vitamins, over the counter, and other nonprescription remedies	DMARD^d^ medication class for all medications taken for the treatment of RA. This attribute serves as confirmation of self-reported RA as well as a baseline covariate.	
	Telephone number (cellular)	—	
	Preference for email versus text notifications and reminders	—	
	Typical work schedule	—	
	Typical sleep schedule	—	
**ePRO^e^ measures**			
	Pain, single-item NRS^f^ (daily/ArthritisPower)	0 (no pain) - 10 (pain as bad as it could be) at 0.5 intervals	
	Fatigue, single-item NRS (daily/ArthritisPower)	0 (no fatigue) - 10 (worst possible fatigue) at 0.5 intervals	
	PROMIS-CAT^g^ Fatigue (weekly/ArthritisPower)	0-100 t-score; 0 - <55 (within normal limits), 55 - <60 (mild), 60 - <70 (moderate), ≥70 (severe)	
	PROMIS-CAT Pain Interference (weekly/ArthritisPower)	0-100 t-score; 0 - <55 (within normal limits), 55 - <60 (mild), 60 - <70 (moderate), ≥70 (severe)	
	PROMIS-CAT Physical Function (weekly/ArthritisPower)	0-100 t-score; ≥55 (within normal limits), 40 - <55 (mild), 30 - <40 (moderate), <30 (severe)	
	PROMIS-CAT Satisfaction with Participation in Discretionary Social Activities (weekly/ArthritisPower)	0-100 t-score; ≥55 (within normal limits), 40 - <55 (mild), 30 - <40 (moderate), <30 (severe)	
	PROMIS-CAT Sleep Disturbance (weekly/ArthritisPower)	0-100 t-score; 0 - <55 (within normal limits), 55 - <60 (mild), 60 - <70 (moderate), ≥70 (severe)	
	OMERACT^h^ RA Flare (weekly/ArthritisPower)	0 (low) - 50 (high)	
	Godin Leisure-Time Physical Activity Questionnaire (weekly/ArthritisPower)	0-23 (insufficiently active), ≥24 (active)	
	Adherence to ePRO measure completion (daily or weekly/ArthritisPower)	Ratio of completed ePROs to number of required ePROs prior to discontinuation or end of study period	
	Persistence with ePRO measure completion (daily or weekly/ArthritisPower)	Days until first incomplete or missing ePRO within study period	
**Passively collected biosensor data (continuous [if smartwatch is synced every <5 days]/Fitabase)**			
	Activity	Steps (minute, hour, day) Activity intensity (minute, hour, day) Distance (day) - units = miles Energy expenditure (minute, hour, day) Metabolic Equivalents (minute)	
	Activity-derived variables	Time walking per day (minutes) Time in activity intensity categories per day (minutes) Active time (minutes) Aerobic time (minutes)	
	Heart rate	Beats per minute (minute, day)	
	Heart rate–derived variables	Time in heart rate zone of interest based on exercise charts	
	Sleep	Time sleeping in last 24 hours (minute, day)	
	Sleep-derived variables	Time in light, deep, and REM^i^ sleep and time to sleep onset, time awake and other derived variables (day)	
	Adherence to wearing and syncing smartwatch	Ratio of days with smartwatch data to number of days during study period prior to discontinuation or end of study period	
	Persistence with wearing and syncing smartwatch	Days until first day without any smartwatch data in Fitabase	

^a^RTA: refuse to answer.

^b^RA: rheumatoid arthritis.

^c^Not applicable.

^d^DMARD: Disease-Modifying Antirheumatic Drug.

^e^ePRO: electronic patient-reported outcome.

^f^NRS: numeric rating scale.

^g^PROMIS-CAT: Patient-reported outcome measurement information system-computer adaptive testing.

^h^OMERACT: Outcome Measures in Rheumatology.

^i^REM: rapid eye movement.

#### Main Study Period

Upon successful completion of the lead-in period, participants will receive a Participant Kit that will contain a smartwatch, on-boarding and training materials, and instructions to access study resources such as frequently asked questions, training videos, and research team contact information. Participants will receive reminders as smartphone lock-screen notifications and as emails to sync their smartwatch data and complete their ePROs during the subsequent 84 days. To avoid sending extraneous notifications to those participants who are consistent in smartwatch data download, syncing, and ePRO completion, ArthritisPower will use the daily Fitbit and ePRO data to provide targeted text, email, and phone follow-up reminders, as well as support to participants whose data are missing for one or more days.

#### Lead-Out Period

Following the main study period is a three-month lead-out period, during which no reminders to sync the smartwatch will be sent and no ePRO collection will be prompted beyond normal monthly reminder emails that are sent to all participants in the ArthritisPower registry. The purpose of the lead-out period is to assess the effect of reminders on the main study, observe the attrition in smartwatch use, and assess any changes in smartwatch measures when not actively solicited.

#### Pilot

The study will begin by enrolling a pilot cohort of 10-20 participants who will provide feedback about their experience during the lead-in period and initial setup for the main study period. Participant feedback during the pilot will allow for operational adjustments to be made prior to the larger study start. Participants will provide feedback via emailed questionnaires and phone calls on various logistical aspects, including receiving and completing ePRO measures via the smartphone app, getting a shipped package (Participant Kit) containing the smartwatch, and setting up the smartwatch. This feedback will be used to adjust the smartwatch provisioning process as needed. Any major proposed adjustments would be submitted to the Institutional Review Board for review and approval prior to implementation.

### Study Population

GHLF will send eligible members of the ArthritisPower research registry an invitation to participate in this study. Participants within the ArthritisPower registry are eligible to join this study if they provide informed consent and meet each of the inclusion criteria listed in Textbox 1.

### Compensation

Participants who complete all activities for the first 4 weeks of the main study period will receive a US $25 gift card, and those who complete all activities for all 12 weeks of the main study period will receive an additional US $50 gift card.

### Data Collection

Participants who successfully complete the 14-day lead-in period will be issued a smartwatch that will be used to collect digital measures of activity, heart rate, and sleep. The participants are not required to return their smartwatch at the end of the study. Day 0 of the study is the date that the first smartwatch data will be observed from the participant. The following day is Day 1 for analysis purposes, as it will constitute a full 24-hour period of data collection.

### Variables and Measures

Table 1 presents the study variables and their operational definitions. The t-score used to measure the Patient-reported outcome measurement information system-computer adaptive testing (PROMIS-CAT) is a standardized score based on the overall (healthy) US population where 50 is the average (mean), which allows us to see how much above or below (ie, number of standard deviations) a person’s PROMIS-CAT ePRO deviates from the mean.

### Data Workflow

GHLF will send eligible members of the ArthritisPower research registry an invitation to participate in this study. Once enrolled, participants will provide daily and weekly survey data to be stored in the ArthritisPower database. During the main study period, participants will be equipped with preconfigured Fitbit accounts linked by GHLF to the Fitabase platform. The Fitabase platform will stream the participants’ activity metrics directly from the Fitbit cloud. This will allow the research team at GHLF and UAB to monitor participant sync and charge activity and send participation reminders. Accessing Fitabase via an exposed application programming interface enables automation of this process.

Identifying information will be collected separately from survey responses and digital measures of activity, heart rate, and sleep to protect participant privacy and maintain a deidentified data set. All identifying information collected will be handled by internal ArthritisPower research staff, as per guidelines specified in ArthritisPower protocol. All data collected through this study will be analyzed, stored, and collected by ArthritisPower staff at GHLF and UAB. Individual identities will only be used by ArthritisPower staff at GHLF and UAB to send smartwatches and follow up with participants to troubleshoot problems with data collection or syncing. Any results will be reported in a deidentified or aggregated form. All information will be stored and protected in password protected files and can only be accessed by the ArthritisPower research team. The only participant-level data that will be shared with Eli Lilly and Company is the deidentified smartwatch data to enable greater understanding of passively collected smartwatch data. It will not be possible for the research team at Eli Lilly and Company to contact participants for this study. Any identifying information collected will not be included in any notes or report documents used by the team. Data flow throughout the study is outlined in Figure 2.

Inclusion criteria for the DIGITAL study.Age 19 or olderUS residentSelf-reported diagnosis of rheumatoid arthritisRegistered a valid email address with ArthritisPowerCurrently being seen by a US rheumatologistCurrently taking at least one conventional synthetic or targeted disease-modifying antirheumatic drug for rheumatoid arthritis, but not baricitinibOwn a smartphone (iPhone 4S and later or Android 4.3 and later) to which they have downloaded the ArthritisPower appAre willing to contribute daily and weekly ePROs for up to 98 days, and health activity tracker data for at least 84 daysAre willing to wear the smartwatch while sleepingWill not be out of internet access (Wi-Fi or mobile data) for 4 or more consecutive days during the studySuccessfully complete the lead-in periodAre willing to be contacted by e-mail or phone by a study coordinator if they fail to adhere to the study protocol

**Figure figure2:**
[figure not shown]
Study data workflow.

### Analyses

#### Primary Analyses: Agreement Between ePRO and Passively Collected Digital Measures

The primary objective of this study is to quantify the agreement between passively collected digital measures (eg, activity) and ePRO data (eg, pain NRS scores). Descriptive statistics will summarize the demographics and baseline characteristics for all enrolled participants. The primary analysis will be a descriptive summary of the correlation between passively collected biosensor data and ePRO data. See Table 1 for a list of the ePRO and passively collected digital measures. For ePROs assessed weekly, multiple summary measures of the passive measures will be created over the corresponding weekly timeframe. Summaries to be explored include the average over the time period, trends, most recent, minimum, maximum, variation, and transformations in the data. Correlations between the ePRO and passive measures will be quantified using both a simple correlation matrix for each week as well as using repeated measures models over the entire study. Repeated measures models will be implemented using each ePRO as the outcome measure, with time (eg, week as a classification factor), baseline measures, and the various passive measures as potential factors in the model. The starting model will be a simple main effects model, and then a penalized regression model will also be used to optimize model selection, including the potential for 2-way interactions (including with time). This will allow for assessment of changes in correlations over time adjusted for participant level covariates.

For digital measures obtained daily, a repeated measures model will assess the association between the ePRO (outcome) and passive measures over time (with day as the time period of assessment rather than week). Daily ePRO data may lag by a day if it is observed that most participants are responding in the morning. Due to the large number of days in the study, time will be considered a numeric variable in this model.

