## Introduction

As the selection and availability of consumer-grade digital technology to measure biometric and activity outcomes have increased dramatically in recent years, their use in clinical and observational studies have also grown. At a minimum, biosensor technology typically measures heartbeat, activity, and sleep, yet these tools have been used primarily in research in disease states with core symptoms that are clearly directly measurable using such technology (eg, Parkinson’s disease) [1]. An individual’s level of activity and sleep quality can be affected by many other conditions, such as migraine, diabetes, systemic lupus erythematosus, atopic dermatitis, obesity, and arthritis. The ability to observe symptom changes in real time (particularly in response to pharmacotherapy and behavior changes) using mobile biosensor technology has the potential to significantly enhance treatment of chronic disease by enabling more rapid and focused deployment of interventions.

Rheumatoid arthritis (RA) is the most common autoimmune inflammatory arthritis and often results in joint damage that, without adequate treatment over time, may lead to disability, pain, limitations in physical function, and other impairments important to patients [2]. Treating clinicians typically see RA patients at 3- to 6-month intervals. Assessments at clinician visits are necessary, but not enough, to understand the full spectrum of a patient’s clinical state, progression, and the waxing and waning nature of their symptoms. The true severity of pain and flares experienced between visits may not be captured at office visits due to recall bias. To understand the extent of RA disease activity, especially attributes related to pain and stiffness, it is essential to collect patient-reported outcome (PRO) measures in a low-burden, continuous frequency instead of an episodic frequency. PRO measures may include health-related quality of life, physical function, fatigue, sleep, mental health status, work productivity and work activity impairment [3].

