## Discussion

The primary objective of this study is to evaluate the relationship between passively collected digital measures related to activity, heart rate, and sleep, collected from a smartwatch, with ePROs related to pain, fatigue, physical function, RA disease activity, and flare among people living with RA over 3 months. Since passively collected data, such as step counts and heart rate, are measured in a more continuous and objective manner than ePROs, there are implications for both research and patient care depending on the strength of the correlation between these two types of data.

For research, remote data collection of trial participants could minimize participant burden and save time and money required for clinical trials due to less frequent clinical visits and fewer staff hours. Among patients, both activity trackers and remote collection of ePROs mitigate recall bias and offer the opportunity for more comprehensive data collection. Our findings may help inform future studies by identifying when ePRO data are necessary to supplement passive data and when they are not. Collecting data during the interim period between clinician visits is important for patients with RA because each day can be different, so tracking variability in how the disease behaves day-to-day may help better assess disease activity. If ultimately accepted by regulators, this could lead to greater precision and thus smaller clinical trials, resulting in more rapid approval of medications for the marketplace. Moreover, this information facilitates a quicker and more continuous stream of real-world data being generated for comparative effectiveness research. As such, the type of approach represented in this protocol might be integrated into a complete, patient-centric digital health solution and bundled with a medication prescription, a so-called Beyond the Pill approach [21]. As a result, patients and clinicians may benefit from new information about therapies that are equally or more effective using data collected outside of a typical clinical setting. It could, for example, inform management of RA patients on combination therapy who are doing well (eg, in remission) and might consider discontinuing use of a drug without negatively affecting disease activity and symptoms.

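### The weekly correlation matrices are between-person only and the weekly model blends two associations, so on their own they do not show that the watch follows change within a participant

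*Protocol article*

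**What the plan says.** Under Primary Analyses the protocol article states the aim: "The primary objective of this study is to quantify the agreement between passively collected digital measures (eg, activity) and ePRO data". Correlations are to be "quantified using both a simple correlation matrix for each week as well as using repeated measures models over the entire study". The models are specified as "Repeated measures models will be implemented using each ePRO as the outcome measure, with time (eg, week as a classification factor), baseline measures", followed by "and the various passive measures as potential factors in the model". They start from main effects only; a penalized regression then selects terms, including two-way interactions. For daily data, "a repeated measures model will assess the association between the ePRO (outcome) and passive measures over time", with day as a numeric time variable.

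No person mean, person-centred deviation, change-on-change term or within-person correlation is stated for these analyses, and no random-effect or covariance structure is given. Sample Size and Statistical Methods bases power on a correlation at a single time point, which is a comparison across participants.

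The intended use includes change over time. The Abstract raises the possibility of watch data standing in for, or complementing, reported symptoms. The Discussion says that "tracking variability in how the disease behaves day-to-day may help better assess disease activity" and lists flare detection and judging treatment effectiveness between visits as possible benefits.

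**The concern.** Two different questions sit under the word agreement. One is whether participants who walk more, or sleep longer, report less pain than other participants. The other is whether a participant reports more pain in weeks when their own step count falls below its usual level. Stable differences such as age or body weight can produce the first association without the second.

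A matrix computed separately for each week answers only the first question. A repeated-measures model with one uncentred term per passive measure returns a weighted average of the two slopes, with weights set by the variance components, the number of occasions and the covariance structure. The reader cannot tell from that coefficient which association produced it.

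The risk runs both ways. A watch that carries no information about change in a patient could show clear weekly correlations, and a watch that does follow change could show weak ones. The Discussion links the implications for research and care to the strength of the correlation, including when ePROs are needed and when they are not. The distinction therefore bears on the conclusions.

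**Working it through.** **Inputs from the article.** 250 recruited, at least 75% completing most measures: 0.75 × 250 = 187.5, taken as 187. The main period is 12 weeks (84 days).

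**Assumptions.** The article gives no ICCs, slopes or alpha level. Two-sided alpha 0.05 is assumed throughout.

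**1. The plan's own power figure.** Power = Φ(atanh(r)·√(n−3) − 1.96).
- r = 0.2: 0.2027 × 13.565 − 1.96 = 0.79, power 78.5%.
- r = 0.3: 0.3095 × 13.565 − 1.96 = 2.24, power 98.7%.

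The stated figures (at least 80%, over 90%) are reproduced to within 2 points. They describe one cross-sectional correlation, not tracking within a person.

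**2. What a single-week correlation contains.** r_week = r_between·√(ICCx·ICCy) + r_within·√((1−ICCx)(1−ICCy)). With both ICCs at 0.8:
- r_between 0.3, r_within 0: 0.3 × 0.8 = 0.24, detected with 91% power although nothing is tracked.
- r_between 0, r_within 0.3: 0.3 × 0.2 = 0.06, detected with 13% power although change is tracked.

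With both ICCs at 0.7 the two values are 0.21 and 0.09.

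**3. Weekly correlation in the slope scenario.** Digital measure with variance 1, between-person slope -0.5, within-person slope 0, random-intercept SD 0.7, residual SD 0.6.
- ICC 0.8: covariance -0.5 × 0.8 = -0.40; ePRO variance 0.25 × 0.8 + 0.49 + 0.36 = 1.05; r = -0.40/√1.05 = -0.39.
- ICC 0.6: covariance -0.30; ePRO variance 0.15 + 0.49 + 0.36 = 1.00; r = -0.30.

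**4. Blended slope in the weekly model.** For a random-intercept model with 12 weeks, information per person at ICC 0.8 is:
- within: 11 × 0.2/0.36 = 6.11;
- between: (0.8 + 0.2/12)/(0.69 + 0.36/12) = 0.817/0.72 = 1.13. Here 0.69 = 0.49 + 0.25 × 0.8, because the between-person signal left unexplained enters the intercept variance.

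The between-person weight is 1.13/7.25 = 16%. The slope across person means is -0.40/0.817 = -0.49, so the blended slope is about -0.077. The same steps at ICC 0.6 give a weight of about 7% and a slope of about -0.034.

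Simulation (187 people, 12 weeks, 80 runs per scenario, no baseline covariates):

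| ICC | Blended slope | Significant |
|---|---|---|
| 0.8 | -0.076 | 75% |
| 0.6 | -0.037 | 44% |

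At ICC 0.8, the model with separate mean and deviation terms gave -0.50 between and 0.01 within, with the within term significant in 6% of runs.

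**5. With baseline ePRO in the model.** A second simulation used ICCs of 0.7 to 0.8, r_between -0.4 and r_within 0, with 30 runs per scenario (rates good to about ±18 points).
- Uncentred slope -0.04 to -0.06, significant in 40% to 67%.
- With baseline ePRO added: -0.03 to -0.04, significant in 20% to 57%.
- Within term after the split: significant in 0% to 10%.

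**6. When tracking is real.** With a true within-person slope of -0.30 to -0.37 and no between-person association, the uncentred random-intercept model gave -0.28 to -0.33 (-0.23 to -0.27 with baseline ePRO) and was significant in every run. An independence fit with baseline ePRO gave only -0.05 to -0.10.

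**7. Daily model.** The set-up of step 4 with 84 days at ICC 0.8 has within information 83 × 0.2/0.36 = 46.1 and between information 0.802/0.694 = 1.16. The weight is 1.16/47.3 = 2.4% and the slope about -0.012. A simulation gave -0.012 (significant in 23%) at ICC 0.8 and -0.005 (10%) at ICC 0.6.

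**The case against.** The strongest reply is that the stated objective is agreement, described as a descriptive summary of correlation, and that within-person tracking is not named as the target. The Introduction sentence "The ability to observe symptom changes in real time" is a general remark about biosensors in chronic disease, and the Discussion speaks of possible implications. This stands in part. Agreement in level between participants is a legitimate result, and a reader who inferred that only the within-person slope matters would go beyond the article.

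A reader might also infer that the planned models cannot show tracking at all. Steps 4 and 6 do not support that. With a random intercept, the weekly slope is mostly within-person information and real tracking is detected; in the daily model the mixing is only a few per cent of the weight. Baseline measures, which the plan includes, reduce it further. Moreover, a slope of -0.04 to -0.08 would hardly be read as a good proxy, so the significance rates overstate the practical harm.

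A third reply is that predictor coding and covariance structure belong in the SAP, and that the summaries to be explored include trends, variation and transformations. The article may indeed leave the covariance to the SAP. The weekly matrix, however, is cross-sectional whatever the SAP adds, and the article does list the model's factors.

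Finally, Secondary Analyses has within-person elements: test-retest correlations when the ePRO is stable, prediction models using earlier changes, and three-day pre-flare summaries. They bear on change over time, but none estimates the within-person association between watch and ePRO.

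**Conclusion.** The point holds for the weekly analyses. The week-by-week matrices are between-person results, and the weekly model as described reports one coefficient for two associations. Neither shows by itself that the watch follows a participant's symptom changes, and the article does not say which association would support a proxy conclusion.

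The matrix can mislead substantially in either direction: a correlation of -0.30 to -0.39 with no tracking, or 0.06 with an assumed within-person correlation of 0.3. The distortion in the weekly slope is modest in size but enough to produce frequent significant results, and under a random intercept it is small in the daily model. The matrix identity is exact given the ICCs. All ICCs, slopes and the zero within-person effect are assumptions, and the mixing in the models depends on a covariance structure the article does not give.

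The documents do not support the reading that the primary analysis is uninformative about tracking, or that between-person agreement is irrelevant.

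**What to change.** In the weekly model, and for consistency in the daily one, replace each passive measure by two terms: the participant's own mean over the main study period, and the deviation of that week or day from it. Report both coefficients. Use the within-person coefficient for any statement that the watch tracks symptom change, and present the between-person coefficient separately as agreement in level. Label the weekly matrices as between-person. State in the SAP which association supports which conclusion, and name the covariance structure.

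The cost is two derived variables and one extra model term per measure, plus a few lines of text. No new data and no change to the sample size are needed.
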